## Abstract

**Introduction:**

Depression is a common mental health disorder during pregnancy, with important consequences for mothers and their children. Despite this, it goes undiagnosed and untreated in many women attending antenatal care. Smartphones could help support the prompt identification of antenatal depression in this setting. In addition, these devices enable the implementation of ecological momentary assessment techniques, which could be used to assess how mood is experienced during pregnancy. With this study, we will assess the feasibility of using a bespoke mobile application (app) running on participants’ own handsets for the longitudinal (6 months) monitoring of antenatal mood and screening of depression.

**Methods and analysis:**

We will use a randomised controlled study design to compare two types of assessment strategies: retrospective + momentary (consisting of the Edinburgh Postnatal Depression Scale plus five momentary and two contextual questions), and retrospective (consisting of the Edinburgh Postnatal Depression Scale only). We will assess the impact that these strategies have on participant adherence to a prespecified sampling protocol, dropout rates and timeliness of data completion. We will evaluate differences in acceptance of the technology through a short quantitative survey and open-ended questions. We will also assess the potential effect that momentary assessments could have on retrospective data. We will attempt to identify any patterns in app usage through the analysis of log data.

**Ethics and dissemination:**

This study has been reviewed and approved by the National Research Ethics Service Committee South East Coast—Surrey on 15 April 2016 as a notice of substantial amendment to the original submission (9 July 2015) under the Research Ethics Committee (REC) reference 15/LO/0977. This study is being sponsored by Imperial College London under the reference number 15IC2687 and has been included in the UK Clinical Research Network Study Portfolio under the Central Portfolio Management System number 19280. The findings of this study will be disseminated through academic peer-reviewed publications, poster presentations and abstracts at academic and professional conferences, discussion with peers, and social media. The findings of this study will also inform the PhD theses of [name] and KD.

Strengths and limitations of this studyThis study will explore (1) the role of mobile technology as a medium to address some of the practical barriers preventing depression screening in antenatal settings; (2) how mood and depression are experienced throughout pregnancy (using momentary, experiential and ecological data) and (3) two critical success factors for the successful deployment of mobile technology in pregnancy: user engagement and adherence to a proposed sampling protocol.This study will provide baseline information regarding the appropriateness of a sampling protocol (in terms of its duration, intensity and frequency) for the monitoring of mood and screening of depression during the antenatal period.The technology used in this study has been specifically designed and developed to fit within the clinical context and the local care pathways in which it will be deployed.This study focuses on mood and antenatal depression. It does not consider other common mental health disorders that occur during pregnancy, or the presence of potential triggers or risk factors (eg, domestic violence).The mood-related momentary questions used in this study have not been validated.

## Introduction

Antenatal depression is one of the most common mental health disorders during pregnancy.^1–4^ Point prevalence estimates vary between 7% and 12% (depending on the trimester), and period prevalence estimates suggest that as many as 12.7% of pregnant women could experience an episode of major depression.^3 5^ Moreover, antenatal depression is associated with long-term adverse health outcomes in both mothers and their offspring. Pregnant women suffering from depression are more likely to engage in unhealthy practices (including poor diet, substance abuse and failure to enrol in prenatal care), and are at increased risk of self-harm (or suicide) and postpartum depression.^1 6^ Antenatal depression can also affect fetal development, and has been identified as an independent risk factor for a child’s behavioural, cognitive and emotional development (including through adolescence).^1 7–9^

Research indicates that there is no difference in the prevalence or incidence of depression between pregnant and non-pregnant women.^10^ However, the rate of diagnosis and treatment might be lower in pregnant women.^10^ Approximately three-quarters of pregnant women meeting the diagnostic criteria for depression (and anxiety) are not identified, and only 1 in 10 of those who require further treatment is able to access it.^11^ Some of the barriers to the prompt diagnosis of this disorder include difficulties in differentiating depressive symptoms from the expected mood and somatic changes of pregnancy, stigma, lack of reassurance that mental healthcare is a normal part of antenatal care, characteristics of healthcare providers, configuration of health services, insufficient consultation time and the cost-effectiveness of screening practices.^10–12^

As with other mental health conditions,^13–16^ smartphones could help address some of the practical barriers and facilitate the screening and monitoring of depression throughout the antenatal period. The computational capabilities of these devices allow them to implement validated screening scales (usually retrospective self-reports) at any frequency and for any duration. Smartphones are also able to support the implementation of techniques for the collection of momentary, experiential and ecologically valid data. Being collected in real time, momentary data are less susceptible to many of the biases common to retrospective scales (eg, recall bias) and are more sensitive to fluctuations over time.^17–19^ The networking capabilities and wide availability (approximately 71% of UK adults)^20 21^ of smartphones, and the software development and distribution framework of mobile applications (apps), could help practitioners to circumvent some of the practical challenges associated with screening and clinical monitoring, and reduce the costs associated with data handling and management.

Altogether, these characteristics could contribute to making the screening and monitoring of antenatal depression more cost-effective: an initial resource-intensive app development phase would be followed by a relatively low-cost, large-scale distribution of the app onto patients who own smartphones. Thereafter, regular depression assessments could take place remotely, at anytime and anywhere (further comprehensive clinical assessments and the provision of treatment being dependent on local referral and care pathways). Nonetheless, the feasibility of using smartphones for this purpose needs to be explored.

In this area of research, a key factor is the patient’s willingness to run screening or clinical monitoring apps on their personal handsets.^16^ This could influence patient compliance with clinician-led data gathering (sampling) protocols, and thus affect data completeness. The latter refers to the minimum amount of information required by clinicians to inform their decisions, and is an important data quality dimension in healthcare.^21^ Data completeness is also susceptible to the burden that the intensity of sampling protocols (both in terms of frequency and duration) can place on patients, as well as on the value that patients might derive from the data collected. Moreover, the impact that adding momentary assessments can have on retrospective data also needs to be explored, as this could lead to more efficient diagnostic and therapeutic decisions.

This study is part of a project aimed at understanding the role of mobile technology for the screening and assessment of antenatal depression and psychological well-being in the context of antenatal care pathways in the National Health Service (NHS) in the UK. A previous feasibility study assessed the feasibility of using iPads in the waiting area of antenatal clinics for implementing the National Institute for Health and Care Excellence (NICE) recommendations for the recognition of depression.^22^ The present study will explore the feasibility of using a bespoke app to support the longitudinal and remote assessment of mood and depression screening throughout the antenatal period. We will evaluate issues of patient acceptance (namely, adherence to sampling protocols and dropout rates) by comparing two 6-month sampling protocols requiring either (1) monthly retrospective *and* momentary assessments or (2) monthly retrospective assessments.

## Methods and analysis

### Study design

We will assess the feasibility of using a bespoke mobile application, called BrightSelf, running on participants’ own smartphones to assess and monitor depression and mood during the antenatal period through a combination of retrospective assessments and ecological momentary assessments (EMA).

We will use a parallel, randomised controlled study design to assign our participants to one of two types of assessment strategies:Retrospective plus momentary assessment: requiring the completion of (1) the Edinburgh Postnatal Depression Scale (EPDS), (2) five momentary questions (assessing a participant’s mood, sleep, worry, enjoyment and energy levels), and (3) two contextual questions once a month for 6 monthsRetrospective assessment: requiring the completion of the EPDS once a month for 6 months.

### Sample selection and recruitment

We will select our sample of participants from women attending antenatal clinics in general practices, community services and secondary care NHS centres in England during their first 14 weeks of pregnancy. We have chosen this limit to ensure that most assessments will occur during pregnancy.

On the day of their antenatal appointment, each potential participant will be approached by a clinical studies officer (CSO) or a research midwife with appropriate good clinical practice training, and will be provided with a participant information sheet. Potential participants expressing their interest in taking part in this study will be assessed against our inclusion and exclusion criteria (table 1).

**Table 1 T1:** Participant inclusion and exclusion criteria

**Inclusion criteria**	**Exclusion criteria**
Women who are 18 years old or older	Current diagnosis of depression or other mood disorder made by a health professional
Up to 14 weeks pregnant (assessed through a dating ultrasound scan)	Currently receiving treatment for depression or other mood disorder (whether it is talking therapies or pharmacological treatment)
Any parity	Recent personal history of depression or other mood disorder in the past 12 months
Attending antenatal clinics in participating National Health Service sites	Not comfortable reading and writing in English
Own smartphone (either an iPhone or any type of Android handset)	Not owning a smartphone, or owning an incompatible handset (ie, Windows Phone, Blackberry or Linux)

Potential participants meeting our inclusion criteria will have all the study details explained to them, and will be given the opportunity to ask as many questions about the study as they need. Potential participants will have a minimum of 24 hours to decide on participation; refusal to take part in this study will not have an impact on their legal rights, medical care or their relationship with care providers.

We will obtain written informed consent from those potential participants who, after receiving all the relevant study information and having all their questions answered to their satisfaction, still wish to take part in this study.

After obtaining consent, participants will be asked to self-complete a baseline assessment using a tablet computer. This assessment will consist of a (1) sociodemographic survey, (2) the Whooley questions and (3) the EPDS (see online supplementary appendix 1). The last two instruments are recommended by the NICE to screen for depression during pregnancy.^23^ Subsequently, the CSO or research midwife will guide participants through the process of downloading (from either the Apple AppStore or Google Play Store) and installing BrightSelf onto their own handsets. To this end, they will be able to use a recruiter booklet provided by the central research team (see online supplementary appendix 2). In order to activate the app, participants will need to enter a nine-digit activation code, which will also be provided by the central research team.

10.1136/bmjopen-2016-014469.supp1Supplementary appendix 1

10.1136/bmjopen-2016-014469.supp2Supplementary appendix 2

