### Randomisation

We will use block randomisation procedures (with blocks of four) to allocate participants to one of the two experimental arms. Random numbers will be generated using Stata V.14.^31^ Each consecutive number will be embedded within the nine-digit activation codes that will be distributed to each participating NHS site. The full activation codes will be generated in the same order in which the random numbers were generated. Each NHS site will receive a list of activation codes on a first-come-first-served basis. Members of the local research teams will not be informed of the random sequence generation and will not be able to identify which number determines participant allocation. They will be required to use activation codes sequentially, as participants are recruited. Activation codes referring to the *retrospective plus momentary assessment* condition will activate a version of BrightSelf in which both the *Check Back* and the *Check In* features are active. Activation codes referring to the *retrospective assessment* condition will activate a version of BrightSelf in which only the *Check Back* feature is active.

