### Outcomes

#### Adherence to sampling protocols

We will calculate the number of participants who complete 100% of the expected assessments (as per the study protocol) as a proportion of the total number of participants who were randomised into the study. We will subdivide this outcome by using the total number of participants who complete the 6-month participation period as the denominator.

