### Data analysis plan

#### Descriptive statistics

We will report the number of potential participants who were eligible and refused to take part in the study. Where possible, we will report the reasons for refusing to participate.

For each experimental group, we will report the following information:Demographic characteristics (as captured by the non-validated, sociodemographic survey)Proportion of participants answering Yes to any of the Whooley questions during the baseline assessmentProportion of participants scoring at each interval of the EPDS: between 0 and 9 points, between 10 and 12 points, and 13 points or above during the baseline assessmentProportion of participants scoring 1 or more points on question 10 of the EPDS during the baseline assessment.

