#### Inferential statistics

We will compare the *retrospective and momentary assessment* and the *retrospective assessment* experimental groups for differences in adherence rates, dropout rates and timeliness of data completion. For this we will use a t-test or the non-parametric equivalent.

We will compare acceptance between the two experimental manipulations by assessing differences in participants’ rankings to those questions on a 7-point Likert scale of the poststudy acceptance survey. We will also conduct a thematic analysis of the open-ended questions of this survey.

In relation to the momentary assessments, we will examine the distribution of delays between the time of notification and time of report in order to assess the effect of this delay on the ecological validity of reports.

We will analyse usage patterns through regression modelling of log data. We will analyse participants’ momentary and retrospective assessments through time-based analyses or multilevel modelling.^33 34^ We will attempt to compare if the momentary assessments had any effect on the retrospective assessments by comparing the EPDS responses given on day 1 to those given on day 6.

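### Baseline EPDS is collected before allocation takes effect but is named only for a descriptive table; using it with arm in the planned EPDS model would give a more precise randomised answer at no cost

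*Protocol article*

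**What the plan says.** Under Sample selection and recruitment, the EPDS is taken between consent and app installation: "After obtaining consent, participants will be asked to self-complete a baseline assessment using a tablet computer". On its content: "This assessment will consist of a (1) sociodemographic survey, (2) the Whooley questions and (3) the EPDS". Under Randomisation, "We will use block randomisation procedures (with blocks of four) to allocate participants to one of the two experimental arms", and the allocation is embedded in the activation code entered later. The baseline score therefore precedes the point at which allocation takes effect, in both arms.

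Under Descriptive statistics the score appears only in a table by arm, as three score bands plus item 10: "For each experimental group, we will report the following information".

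Under Inferential statistics the arms are compared as "experimental groups for differences in adherence rates, dropout rates and timeliness of data completion", and the method is given: "For this we will use a t-test or the non-parametric equivalent". EPDS and momentary data go to time-based analyses or multilevel models, with no covariates named either way. For the abstract's aim, "We will also assess the potential effect that momentary assessments could have on retrospective data", the one contrast named is EPDS on day 1 against day 6 of an assessment period.

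**The concern.** A woman's later EPDS can be expected to follow her own usual level, so her baseline score is the natural covariate for any comparison of EPDS between arms. The article names no such comparison. Day 1 and day 6 exist only in the retrospective plus momentary arm; the other arm has a one-day period with a single EPDS. The named contrast therefore does not use the randomisation. It also cannot separate an effect of the momentary questions from that of answering the EPDS again five days later.

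For adherence, dropout and timeliness, the article does name a test, and that test has no place for a covariate. If baseline mood predicts skipping assessments or leaving, some precision is given up there too. At stake is a sharper answer to a stated aim, from data already in hand.

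**Working it through.** **The plan's own figure.** The inputs under Sample size calculations are 95% confidence and a CI of 10, read here as ±10 percentage points. The adherence rate is not stated; p = 0.5 is assumed as the worst case.
- n = 1.96² × 0.5 × 0.5 / 0.10² = 96.04, which reproduces 96 per arm. Reading 10 as the full width would give 384.
- This is the precision of a single arm's rate, so covariate adjustment does not alter it.

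**Arm difference in one follow-up EPDS.** Linear adjustment for baseline multiplies the standard error by √(1 − r²), where r is the within-woman correlation. The article gives no r; 0.4 to 0.7 is assumed.

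| r | √(1 − r²) | Fall in standard error |
|---|---|---|
| 0.4 | 0.92 | 8% |
| 0.5 | 0.87 | 13% |
| 0.6 | 0.80 | 20% |
| 0.7 | 0.71 | 29% |

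**Arm difference in adherence.** The outcome is yes/no per woman: "We will calculate the number of participants who complete 100% of the expected assessments". With 96 per arm and p = 0.5, the unadjusted 95% half-width is 1.96 × √(2 × 0.25 / 96) = 14.1 points. Here r is the correlation of baseline EPDS with adherence. It is not given; 0.1 to 0.3 is assumed.

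| r | Variance reduction r² | Adjusted half-width, 14.1 × √(1 − r²) |
|---|---|---|
| 0.1 | 1% | 14.1 points |
| 0.2 | 4% | 13.9 points |
| 0.3 | 9% | 13.5 points |

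**Chance imbalance.** In 95% of randomisations the arms' mean baseline EPDS differ by no more than 1.96 × √(2/96) = 0.28 SD (0.25 SD at 125 per arm). At the edge of that range the adherence difference would shift by r × 0.283 × 0.5, that is 1.4, 2.8 or 4.2 points for r = 0.1, 0.2 or 0.3. The 14.1-point half-width already includes this variation.

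**The case against.** The strongest reply is that an article need not list covariates. The analysis plan is not shown, and the multilevel model could take baseline EPDS without contradicting anything in the text. That stands, so silence about the model's covariates is not an error. Two things are stated and not merely left out: a test without covariates for three outcomes, and a one-arm contrast for the EPDS aim.

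A reader might infer more, and the document does not support it:
- **That every arm comparison is fixed as unadjusted.** The named test covers adherence, dropout and timeliness only. Usage logs go to regression, the EPDS series to models with open covariates, and acceptance ratings have no named test.
- **That ignoring baseline EPDS biases the results.** Allocation is random. The unadjusted comparison is unbiased and its standard error allows for chance imbalance.
- **That imbalance between arms could distort the day 1 against day 6 contrast.** Each woman is her own control in that contrast, so it cannot.
- **That adherence, dropout or timeliness would gain as much as EPDS.** The EPDS is not the baseline value of any of them.
- **That averaging all EPDS scores would give a still larger gain.** The arms are scheduled for different numbers, two per period against one (12 against 6 over six periods), so a common mean of six does not describe both.

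It is also fair to say that this is a feasibility study sized on an adherence interval, and that the choice of an adjusted analysis is partly preference.

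**Conclusion.** This is a minor point of efficiency. The comparisons as planned are valid. The part most worth acting on is the EPDS aim, where the only named contrast makes no use of the randomisation although a pre-allocation score is available for a between-arm estimate. The gain is about 8% to 29% of the standard error for one follow-up EPDS, resting on an assumed within-woman correlation of 0.4 to 0.7 and linear adjustment. For adherence, the reduction is about 1% to 9% of variance, resting on assumed correlations of 0.1 to 0.3. The same r² rule applies to dropout and timeliness. The document gives none of these correlations, so the true gain for these three outcomes is unknown and probably small.

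**What to change.** 1. In the multilevel EPDS model already planned, include arm and baseline EPDS total as a continuous covariate. Use EPDS occasions comparable in both arms, for example the first EPDS of each period. The first of these comes before any prompted momentary assessment, so the later periods carry the information. Because the combined arm also has an extra EPDS each period, describe the result as the effect of the whole assessment strategy. Keep day 1 against day 6 as a within-woman supplement.
2. For adherence and dropout (yes/no per woman), prespecify logistic regression with arm and baseline EPDS. For timeliness, use binomial regression on each woman's counts. Report these alongside the unadjusted results.
3. Fix this wording before outcome data are seen.

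The cost is analysis text only. The baseline EPDS is already collected, and neither the sample size nor the burden on participants changes.
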